## **5.5 TREATMENT DATA COLLECTION**

Details of the dose, timing and route of administration of all study medication will be recorded in the eCRFs and treatment charts of study patients by the study team, who will administer or directly observe the administration of all study medication during hospitalisation.

## **5.6 NON-TRIAL TREATMENT**

All non-trial treatment taken by the patient will be recorded at enrolment, at follow-up, and in the event of an SAE occurring.

### **5.6.1 MEDICATIONS PERMITTED**

Drugs not known to be contraindicated with the trial drugs will be permitted.

### **5.6.2 MEDICATIONS NOT PERMITTED**

Fluconazole is contraindicated in combination with cisapride and the class of antihistamines including terfenadine. Other drugs (including cisapride, astemizole, pimozide, quinidine and erythromycin) that have potential to prolong the QT interval should be avoided if possible during the first 2 weeks of treatment.

### **5.6.3 MEDICATIONS TO BE USED WITH CAUTION**

Rifampicin – May reduce fluconazole levels.

### **5.6.4 TREATMENT AFTER TRIAL EVENT**

Treatment will be at the discretion of the responsible physician.

## **5.7 CO-ENROLMENT GUIDELINES**

Co-enrolment in previous or future trials is considered in [Section 4.3 - Co-enrolment Guidelines](#).

## ASSESSMENTS & FOLLOW-UP

During the two-week induction phase patients will initially be admitted and clinical responses monitored daily. Patients may be discharged from day 7, in which case they will receive close outpatient follow-up with daily calls, blood tests as described in the protocol, until they receive a clinic review at day 14. Ongoing outpatient follow-up will be at 4, 6, 8 and 10 weeks. At 10 weeks patients will be transferred into the local ART clinic for continuing management. A single telephonic contact at 16 weeks to assess vital status and simple disability score will be made.

### 6.1 TRIAL ASSESSMENT SCHEDULE

#### i) Clinical response:

Clinical response will be monitored daily for the first 2 weeks, then in follow-up 4, 6, 8 and 10 weeks after start of therapy. A single telephonic follow-up to ascertain vital status and simple disability score will be made at week 16. Every effort will be made (for example with mobile telephone calls and financial help with travelling expenses) to obtain accurate and complete follow-up data for 10 weeks after the start of treatment. Particular attention will be paid to the possibility, in ART-naïve patients, of immune reconstitution reactions after starting ART.

#### ii) Laboratory data:

Day 3, 5, 7, 10, 12, 14: Creatinine, Electrolytes

Day 7, 14: Full blood count, ALT

Week 4 (clinic): Full blood count, Creatinine, Electrolytes, ALT

At the time of monitoring blood tests, and at additional times (see schedule below), an extra 2.5 ml of blood will be taken for PK studies.

Days 7, 14: Follow up CSF examinations (performed by study team) for: opening pressure, quantitative fungal culture, CSF for drug levels, immune parameters.

| TABLE 6.1. Event Schedule         | Screening | Week 1 |    |    |    |    |    |    | Week 2 |    |     |     |     |     |     | Wk 4 | Wk 6 | Wk 8 | Wk 10 | Wk 16 |
|-----------------------------------|-----------|--------|----|----|----|----|----|----|--------|----|-----|-----|-----|-----|-----|------|------|------|-------|-------|
| Study Day                         | ≤D0       | D1     | D2 | D3 | D4 | D5 | D6 | D7 | D8     | D9 | D10 | D11 | D12 | D13 | D14 |      |      |      |       |       |
| Consent forms              |           |        |    |    |    |    |    |    |        |    |     |     |     |     |     |      |      |      |       |       |
| PIS and signed consent            | X         | X      |    |    |    |    |    |    |        |    |     |     |     |     |     |      |      |      |       |       |
| Follow up                  |           |        |    |    |    |    |    |    |        |    |     |     |     |     |     |      |      |      |       |       |
| Screening and randomisation       | X         | X      |    |    |    |    |    |    |        |    |     |     |     |     |     |      |      |      |       |       |
| Clinical review                   |           | X      | X  | X  | X  | X  | X  | X  | X      | X  | X   | X   | X   | X   | X   |      |      |      |       |       |
| Outpatient follow-up              |           |        |    |    |    |    |    |    |        |    |     |     |     |     |     | X    | X    | X    | X     |       |
| Week 16 telephone                 |           |        |    |    |    |    |    |    |        |    |     |     |     |     |     |      |      |      |       | X     |
| Clinical labs              |           |        |    |    |    |    |    |    |        |    |     |     |     |     |     |      |      |      |       |       |
| HIV testing                       |           | X      |    |    |    |    |    |    |        |    |     |     |     |     |     |      |      |      |       |       |
| Pregnancy Test (Urine/Serum) (2)  |           | X      |    |    |    |    |    |    |        |    |     |     |     |     |     |      |      |      |       |       |
| Full Blood Count                  |           | X      |    |    |    |    |    | X  |        |    |     |     |     |     | X   | X    |      |      |       |       |
| CD4 count                         |           | X      |    |    |    |    |    |    |        |    |     |     |     |     |     |      |      |      |       |       |
| ALT                               |           | X      |    |    |    |    |    | X  |        |    |     |     |     |     | X   | X    |      |      |       |       |
| Urea, creatinine and electrolytes |           | X      |    | X  |    | X  |    | X  |        |    | X   |     | X   |     | X   | X    |      |      |       |       |
| Clinical evaluation        |           |        |    |    |    |    |    |    |        |    |     |     |     |     |     |      |      |      |       |       |
| Chest X-ray (1)                   |           | X      |    |    |    |    |    |    |        |    |     |     |     |     |     |      |      |      |       |       |
| CSF                        |           |        |    |    |    |    |    |    |        |    |     |     |     |     |     |      |      |      |       |       |
| Opening pressure                  |           | X      |    |    |    |    |    | X  |        |    |     |     |     |     | X   |      |      |      |       |       |
| Cell count and differential*      |           | X      |    |    |    |    |    |    |        |    |     |     |     |     |     |      |      |      |       |       |
| Protein, glucose*                 |           | X      |    |    |    |    |    |    |        |    |     |     |     |     |     |      |      |      |       |       |
| Routine culture *                 |           | X      |    |    |    |    |    |    |        |    |     |     |     |     |     |      |      |      |       |       |
| India ink examination* (3)        |           | X      |    |    |    |    |    |    |        |    |     |     |     |     |     |      |      |      |       |       |
| Cryptococcal antigen* (3)         |           | X      |    |    |    |    |    |    |        |    |     |     |     |     |     |      |      |      |       |       |
| Quantitative fungal culture       |           | X      |    |    |    |    |    | X  |        |    |     |     |     |     | X   |      |      |      |       |       |
| CSF Drug levels                   |           | X      |    |    |    |    |    | X  |        |    |     |     |     |     | X   |      |      |      |       |       |
| Immune parameters                 |           | X      |    |    |    |    |    | X  |        |    |     |     |     |     | X   |      |      |      |       |       |

\*Part of routine care. 1. If clinically indicated. 2. For women of childbearing age. 3. India ink or cryptococcal antigen required for inclusion

## 6.2 PROCEDURES FOR ASSESSING EFFICACY

All deaths during the study period will be recorded. Cause of death will be clinically ascertained by the study physicians (patients will not receive post-mortems). Mortality by treatment group will be analysed with all-cause mortality within the first 10 weeks as the primary endpoint. Cryptococcal clearance rates will be calculated using summary statistics for each patient: the rate of decrease in  $\log_{10}$  CFU per ml CSF per day derived from the slope of the linear regression of  $\log_{10}$  CFU against time for each patient. A linear regression model will be used to compare mean rates of decline or early fungicidal activity (EFA) for each experimental treatment, giving summary differences with 95%CI and significance levels. We will adjust analyses for potential confounding factors, including baseline fungal load. Disability at 10 weeks will be assessed using two simple questions and a modified Rankin score (Table 1).

Table 6.2.

| The two simple questions                                                                                                                                 |                                                                                                                               |                            |
|----------------------------------------------------------------------------------------------------------------------------------------------------------|-------------------------------------------------------------------------------------------------------------------------------|----------------------------|
| Does the patient require help from anybody for everyday activities? (For example eating, drinking, washing, brushing teeth, going to the toilet.) | Yes/no                                                                                                                        | Yes = Poor outcome         |
| Has the illness left you with any other problems?                                                                                                        | Yes/no                                                                                                                        | Yes = Intermediate outcome |
|                                                                                                                                                          |                                                                                                                               | No = Good outcome          |
| The modified rankin scale                                                                                                                                |                                                                                                                               |                            |
| Grade*                                                                                                                                                   | Description                                                                                                                   |                            |
| 0                                                                                                                                                        | No symptoms                                                                                                                   |                            |
| 1                                                                                                                                                        | Minor symptoms not interfering with lifestyle                                                                                 |                            |
| 2                                                                                                                                                        | Symptoms that lead to some restriction in lifestyle, but do not interfere with the patients’ ability to look after themselves |                            |
| 3                                                                                                                                                        | Symptoms that restrict lifestyle and prevent totally independent living                                                       |                            |
| 4                                                                                                                                                        | Symptoms that clearly prevent independent living, although the patient does not need constant care and attention              |                            |
| 5                                                                                                                                                        | Totally dependent, requiring constant help day and night                                                                      |                            |

\*Grade 0: Good outcome, Grade 1 or 2: Intermediate outcome, Grade 3-5: poor outcome.

## 6.3 PROCEDURES FOR ASSESSING SAFETY

There is considerable experience with L-AmB doses up to 10 mg/kg/d. In a trial of treatment for filamentous fungal infections with 100 patients per arm, daily dosing at 10 mg/kg/d compared with 3 mg/kg/d, for 14 days, was associated with increased nephrotoxicity. However, rates of doubling of creatinine and of hypokalaemia were still only those seen with the use of conventional D-AmB formulation 0.7 mg/kg/d in cryptococcal meningitis. Single dose and intermittent L-AmB at up to 10 mg/kg/d has been very well tolerated. Serum creatinine and potassium will be monitored at predetermined intervals to ensure any adverse effects are recognised early and appropriate management undertaken. .

Proportions of patients in different arms suffering clinical and laboratory-defined side effects will be compared as well as the mean percent change from baseline of laboratory values in the treatment groups. Mortality by treatment group will be analysed by summary statistics and time to event analyses, unstratified and stratified for possible confounding factors. The frequency and severity of any immune reconstitution reactions, the factors associated with occurrence of reactions and the frequency of further AIDS-related illnesses will also be determined. These parameters will be reviewed during the study by the Independent Data Monitoring Committee (IDMC – see [Section 9.4](#))

Throughout the study patients will be closely monitored for signs and symptoms of drug toxicity. All toxicities leading to temporary or permanent discontinuation of the study therapy, and all Grade 3 or 4 toxicity effects will require thorough investigation with relevant clinical and laboratory tests as clinically indicated. These should be repeated until final resolution or stabilization of the toxicity. All symptoms and laboratory findings will be graded according to severity using the modified Division of AIDS toxicity criteria.

In the event that the day 7 lumbar puncture identifies an increase in colony forming units from baseline this must be reported as an SAE. The co-ordinating centre will be responsible for managing this situation on a case-by-case basis.

## 6.4 PROCEDURES FOR ASSESSING PHARMACOKINETICS

Plasma samples to describe the PK of liposomal amphotericin B, and enable the PK-PD of liposomal amphotericin B for CM and the impact of PK variability on outcome to be described, will be collected at the end of infusion, then 3, 6, 8 and 24 hours in a substudy of patients at two Ambition Trial recruitment sites. This will likely be Botswana where PK sampling as described has already been undertaken in the phase II study, plus Blantyre.

In addition, in all Ambition trial patients, two samples will be collected at 6 and 24 hours post infusion for L-AmB levels. The serum pharmacokinetics of fluconazole will also be described. A portion (0.5 mL) of the CSF sample obtained for quantitative counts will be reserved to measure fluconazole concentrations, and thereby estimate the extent of penetration of fluconazole into the CSF. We will not attempt to measure concentrations of amphotericin B in CSF as the drug is concentrated in the meninges and brain and cannot be reliably detected in CSF.

The PK-PD data will be modelled using a population methodology, using the program Pmetrics. The same structural mathematical model as previously described by us and applied to rabbit data will be used. The PK-PD model will enable an in depth understanding of the persistence of amphotericin B within the central nervous system and the resultant antifungal effect. Monte Carlo simulation will enable further insights into the regimen(s) that are associated with maximal antifungal activity including dose of liposomal amphotericin B and the maximum interval that can be utilized in clinical settings.

The ability to fit large PK-PD mathematical models to data from patients will require advanced pharmacometric skills that include PK modelling, modelling of tissue penetration, population PK, pharmacodynamics and Monte Carlo simulation. The co-administration of liposomal amphotericin B with fluconazole will also provide the ability to examine for and model any possible interaction between the two agents. This will require separate fluconazole PK-PD datasets that are currently being analysed by the Antimicrobial Pharmacodynamics and Therapeutics Laboratory in Liverpool. APT has a long track record in fitting combination PK-PD models to define the effect (i.e. synergy, antagonism, additivity) of combination chemotherapy.

## 6.5 OTHER ASSESSMENTS

### 6.5.1 ECONOMIC ANALYSES

The objectives of the economic analysis are to estimate the cost consequences and the cost-effectiveness of short-course L-AmB treatment, compared to current care in five country settings across Sub-Saharan Africa, and to inform policy makers on the attractiveness of the new regimen. The expectation is that the short course:

1. Will show a zero net societal cost change or that there will be societal cost savings from the short L-AmB treatment, reducing hospitalization costs over the trial time horizon.
2. Will be cost-effective in terms of societal and service cost of life years saved within the diversity of Sub-Saharan settings when compared to historical cohorts receiving the current standard treatment regimen in each country.
3. That the economic evidence will support wide-scale implementations.

The health service costs of the regimens will be compared, and used along with the primary endpoint data to perform cost-effectiveness modeling at the Liverpool School of Tropical Medicine.

Information on resource and unit costs will be collected at patient-level through the CRFs, as part of the trial, and through two additional separate country costing studies. Firstly, an empirical cost-consequence analysis will take place, using empirical individual patient data on societal resource use and unit cost based on the results from the costing studies in a total of five countries. Both the societal and health care perspective are chosen, and health service costs including, household cost, treatment cost and hospitalisations in both arms will be compared over the trial period. Next, the costing information will be used in a TreeAge cost-effectiveness model that computes health service cost and number of life years survival. Here the two trial arms will be compared to the results from a recent historical cohort. This approach avoids the stochastic fallacy and will determine if short-course high-dose L-AmB will be as or even more cost-effective compared to the current standard of care.

### 6.5.2 EVALUATION OF THE UTILITY OF BASELINE CRYPTOCOCCAL ANTIGEN TITRE ASSESSMENT BY SEMI-QUANTITATIVE CRAG TESTING AND AN EVALUATION OF THE UTILITY OF DIAGNOSTIC QUANTITATIVE PCR

There are no individualized treatment protocols for the management of cryptococcal meningitis. However, organism load at baseline, as assessed by CFU counts or antigen titre, is known to be a powerful prognostic factor. It is conceivable that an abbreviated course of L-AmB may give equivalent or superior (as a consequence of improved safety profile) results to daily conventional AmB at low, but not at the highest baseline antigen titres. A newly developed point of care, lateral flow, semi-quantitative cryptococcal antigen test is now available from Institut Pasteur and Biosynex. We will use this semi-quantitative test in real time to determine antigen titre at baseline, in blood and CSF, and compare results to the currently established point of care test from IMMY. Secondary trial analyses will include the association of baseline titre with outcome (expected to be strongly correlated); but also exploration of the possibility of a differential treatment response between arms according to baseline titre. If such a differential response was observed this sub-study could provide the rationale for and demonstrate the means for individualized treatment, based on a rapid assessment of antigen load. A novel diagnostic quantitative PCR (DNA and RNA) tool will be also be used in each treatment arm and correlated with quantitative culture counts. We aim to estimate the fungal load and fungal viability in blood and CSF at baseline using the PCR in addition to fungal load kinetics. The objective will be to develop a practical alternative to time consuming quantitative cultures in order to improve detection of fungaemia and fungal burden and to identify the best fungicidal treatments in this and subsequent research studies.

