**Figure 1.** Fall in CSF *C. neoformans* CFU over time in thirty HIV-seropositive, antiretroviral therapy-naïve, patients with first episode cryptococcal meningitis were treated with high dose fluconazole (1200 mg/d for 2 weeks, then 800 mg/d until ART started) plus amphotericin B (D-AmB, 1 mg/kg/d), with routine normal saline and potassium supplementation, for the initial 5 days. The decrease in log CFU per ml CSF per day was calculated for each patient using the slope of the linear regression of log CFU against time. Early fungicidal activity (EFA) is shown as the mean rate of fall in log CFU counts/day. The mean rate of decrease in CFU per ml CSF per day, or early fungicidal activity (EFA), was  $-0.30 \pm 0.11$  log CFU/day calculated over the first 2 weeks of treatment, and  $-0.31 \pm 0.14$  log CFU/day calculated over the first week.

[figure not shown][figure not shown]

**Figure 2 (a).** The pharmacokinetics and pharmacodynamics of amphotericin B against *Cryptococcus neoformans* in a murine model of cryptococcal meningitis. There is hysteresis in the pharmacokinetics in plasma versus cerebrum with concentrations in the latter progressively increasing throughout the experimental period. The administration of an abbreviated regimen results in persistently detectable concentrations in both plasma and the cerebrum, which accounts for the persistent antifungal effect. Data are mean  $\pm$  standard deviation. The solid line is the fit of the mathematical model to the data.

[figure not shown]

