**Secondary:**

1. Early Fungicidal Activity derived from Serial LPs on days 1, 7 and 14.
2. Clinical and laboratory-defined grade III/IV adverse events; median % change from baseline in laboratory defined parameters.
3. PK parameters and PK/PD associations of single high dose L-AmB.
4. Health service costs.
5. All-cause mortality within the first 2 and 4 weeks
6. All-cause mortality within the first 10 weeks (superiority)
7. Rates of cryptococcal relapse / IRIS within the first 10 weeks
8. Disability at 10 weeks measured using a simple two question assessment and modified Rankin Score

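### Section 6.5.2 names only correlation for comparing quantitative PCR with culture, and correlation cannot show that PCR reproduces the clearance slope (EFA) its stated purpose depends on

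*Protocol*

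**What the plan says.** Protocol section 6.5.2 plans a quantitative PCR (DNA and RNA) that will be "used in each treatment arm and correlated with quantitative culture counts". No other comparison of PCR with culture is named. The next sentence adds that the investigators will "estimate the fungal load and fungal viability in blood and CSF at baseline using the PCR in addition to fungal load kinetics". The purpose is to "develop a practical alternative to time consuming quantitative cultures", to detect fungaemia and fungal burden better, and to "identify the best fungicidal treatments in this and subsequent research studies".

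The protocol measures fungicidal activity as a slope. In the earlier cohort shown in section 1.4, Figure 1, the decrease was "calculated for each patient using the slope of the linear regression of log CFU against time"; sections 6.2 and 9.5 use the same definition for this trial. Section 9.2 lists as a secondary outcome "Early Fungicidal Activity derived from Serial LPs on days 1, 7 and 14".

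Section 6.5.2 gives no rule for accepting PCR, no target coefficient, no PCR sampling days and no number of patients. The event schedule (Table 6.1) has no PCR row.

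**The concern.** A measure that is to stand in for culture when treatments are ranked by fungicidal activity has to reproduce the culture slope. Correlation of paired counts does not test that. It is unchanged by any linear rescaling: if PCR log count were exactly 2 + 0.5 × log CFU, r would be 1.00 and every EFA would be halved. Fungal load also varies widely between patients and falls by several log10 over two weeks, and that spread alone produces a high r.

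PCR may detect nucleic acid from organisms that no longer grow, and its signal could then fall more slowly than the viable count. The protocol separates load from viability and plans both DNA and RNA assays, so the question is foreseeable. A high r could then be read as support for PCR-based EFA in later studies although the EFA it gives is too slow.

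**Working it through.** The protocol gives no figure for this comparison, so there is none to reproduce. The check asks how far pooled correlation separates a PCR with the right slope from one with the wrong slope.

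**Inputs from the protocol**
- Sampling days 1, 7 and 14 (section 9.2), so days since the first sample are d = 0, 6, 13. PCR sampling on these days is assumed.
- Mean EFA 0.30 and SD 0.11, "log CFU/day calculated over the first 2 weeks of treatment" (section 1.4, Figure 1, 30 patients). The legend does not label the 0.11; it is read here as an SD.

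**Assumptions not in the protocol**
- Baseline mean 5.0 and SD 1.2 log10; culture error SD 0.3; PCR error SD 0.4 to 0.7 log10.
- PCR starts at the true baseline and falls at k times the culture rate. There is no detection limit.

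**Formula.** Culture is C = b + s·d + e, and PCR is P = b + k·s·d + f. Pooling all paired counts, and writing Q = σs²·mean(d²) + μs²·var(d):

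r = (σb² + kQ) / √[(σb² + Q + σe²)(σb² + k²Q + σf²)]

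- mean(d²) = (0 + 36 + 169)/3 = 68.33; var(d) = 68.33 − 6.333² = 28.22
- Q = 0.0121 × 68.33 + 0.09 × 28.22 = 3.367
- Culture variance = 1.44 + 3.367 + 0.09 = 4.897

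For k = 0.6 the numerator is 1.44 + 0.6 × 3.367 = 3.460, and the PCR variance is 1.44 + 0.36 × 3.367 + σf² = 2.812 (error 0.4) or 3.142 (error 0.7). So r = 3.460/√(4.897 × 2.812) = 0.932, or 3.460/√(4.897 × 3.142) = 0.882.

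| PCR rate as share of culture rate (k) | PCR EFA, log10/day | pooled r, PCR error 0.4 | pooled r, PCR error 0.7 |
|---|---|---|---|
| 1.0 | 0.30 | 0.975 | 0.944 |
| 0.8 | 0.24 | 0.964 | 0.924 |
| 0.6 | 0.18 | 0.932 | 0.882 |
| 0.4 | 0.12 | 0.861 | 0.802 |
| 0.2 | 0.06 | 0.725 | 0.665 |

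A simulation of 400,000 patients at k = 1, 0.6 and 0.2 agrees with the formula to within 0.001. An unbiased but noisy PCR (r = 0.944) and a precise PCR that is 40% too slow (r = 0.932) are almost indistinguishable by r. With baseline SD varied from 0.5 to 1.5, r at k = 0.6 runs from 0.84 to 0.94.

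**What a paired slope comparison would show.** The per-patient difference in EFA at k = 0.6 has mean 0.4 × 0.30 = 0.12 log10/day. Its SD is √[(0.4 × 0.11)² + (0.3² + σf²)/84.67], where 84.67 = 3 × 28.22 is the sum of squares of the sampling days. That gives 0.070 to 0.094.
- 95% limits of agreement, 0.12 ± 1.96 × SD: −0.02 to 0.26 (error 0.4), or −0.06 to 0.30 (error 0.7).
- The number of PCR patients is not stated. With an assumed 50 patients the 95% CI half-width is 1.96 × SD/√50 = 0.019 to 0.026; with 200 it is 0.010 to 0.013.

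A bias of 0.12 would be unmistakable at either size.

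**The case against.** The strongest reply is that the protocol rests no decision on r. It sets no threshold, and its aim is worded as development. The sentence after the correlation plans PCR fungal load kinetics and viability, so PCR slopes will exist and a biased slope could be noticed. The text is a few sentences on an ancillary study, and the detail could sit in a sub-study plan. Most of this stands. What remains is that the one comparison with culture the protocol names does not answer its stated purpose, and no comparison of PCR slopes with culture slopes is written down.

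Three stronger readings are tempting and are not supported.
- A reader might infer that PCR will be accepted or rejected on its correlation. Section 6.5.2 states no such rule; a high r could mislead, but the plan does not commit anyone to act on it.
- A reader might infer that r stays high whatever the slope error. The table shows otherwise: it falls to 0.80 to 0.86 at 40% of the rate and 0.66 to 0.73 at 20%.
- A reader might infer that slope bias would reverse the ranking of treatments. A factor k common to both arms shrinks the EFA difference but keeps its order. Distortion needs a bias that differs by arm. With k = 1 in one arm, 0.5 in the other, equal true EFA and error 0.3 in both methods, per-arm r is about 0.98 and 0.91 to 0.92 while PCR shows a false difference of 0.30 − 0.15 = 0.15 log10/day. That is a possibility to check; nothing in the protocol says it will occur.

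**Conclusion.** The point holds as a minor one. For the use stated in section 6.5.2, correlation with culture counts cannot show that PCR gives the right EFA when the slope bias is moderate: a 40% understatement (0.18 instead of 0.30 log10/day) lowers pooled r only from 0.944–0.975 to 0.88–0.93.

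These figures rest on the assumed baseline spread, assay errors, PCR sampling on days 1, 7 and 14, no detection limit, and the EFA of an earlier 30-patient cohort. The invariance of r to linear rescaling needs none of them. Whether PCR is in fact biased cannot be judged from the protocol. The primary mortality endpoint and the culture-based EFA endpoint are not affected.

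**What to change.** In section 6.5.2, state that in patients with serial paired samples PCR-based and culture-based EFA will be calculated per patient and compared by arm: mean paired difference with 95% CI and limits of agreement, judged against an acceptable difference fixed and justified in advance. State also that the between-arm EFA difference will be reported by both methods.

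Keep correlation as description. Report agreement in level only if PCR is calibrated to the CFU scale, which the protocol does not say. The acceptable difference is for the investigators to justify; the 0.2 log10/day margin in section 1.4 was set for comparing regimens in phase II, not for assay agreement.

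The cost is a few sentences and minor analysis work. PCR kinetics are already planned, but the sampling days and patient numbers are not given, so it should be confirmed that serial paired samples will exist before assuming that no extra assays are needed.
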